## Abstract

**Background:**

Healthy eating can improve the course of type 2 diabetes mellitus (T2DM) considerably. As changing eating behaviors in everyday is challenging, there is a need for a nutritional strategy with an eye for everyday life of people with T2DM. A theory centered around the everyday life context is salutogenesis. Salutogenic principles have been operationalized in a new nutritional program for T2DM on food literacy and well-being: the Salutogenic Intervention for Type 2 Diabetes (SALUD) program.

**Objective:**

This study aims to describe the protocol of the invention study that will examine the quantitative and qualitative effects of the SALUD program.

**Methods:**

A semiblinded randomized controlled trial will be performed in the Netherlands. A sample size of 56 (including a 30% dropout rate) people with T2DM has been calculated, of whom half (n=28, 50%) will follow the SALUD program (intervention) and half (n=28, 50%) will receive usual care (control). Recruitment strategies consist of advertisement via local health care professionals, posters, social media, and local newspapers. The SALUD program consists of 12 weekly web-based group sessions under the supervision of a certified lifestyle coach. Fidelity of the delivery is guaranteed by selecting a salutogenic coach, use of an intervention manual, training of the coach, weekly evaluation forms, and recording several sessions. The theoretical salutogenic principle of the intervention is mobilizing 2 important psychosocial resources required for organizing healthy eating in everyday life: self-identity and social support. Measurements will be performed at 3 times: at baseline (T0), after 12 weeks (postintervention; T1), and after 24 weeks (follow-up; T2). The primary outcome is food literacy, measured with the self-perceived food literacy scale questionnaire (expected effect size=0.9). Secondary outcomes are self-efficacy, quality of life, sense of coherence, diet quality, body weight, BMI, and waist-hip ratio. All outcomes will be tested with linear mixed models, following an intention-to-treat approach and standard principles of randomized controlled trials. In addition, a qualitative analysis will be performed.

**Results:**

The proposed study will provide useful information on the effects of a salutogenic program on healthy eating and well-being in people with T2DM in everyday life. Recruitment started on October 1, 2021. The intervention participants followed the SALUD program between January and August, 2022. The acquisition of the data was completed on August 1, 2022; publications are expected in 2023.

**Conclusions:**

This study will be one of the first salutogenic interventions for T2DM, which will provide valuable information on what salutogenic intervention entail. The SALUD program may serve as a concrete, web-based tool. The combination of quantitative and qualitative measures allows a comprehensive evaluation of effects. These insights can be used for further optimalization of T2DM interventions.

**Trial Registration:**

Netherlands Trial Registry, NL8963; https://trialsearch.who.int/Trial2.aspx?TrialID=NL8963

**International Registered Report Identifier (IRRID):**

DERR1-10.2196/40490

## Introduction

### Background

Healthy eating is important for the disease course and quality of life (QoL) of people with type 2 diabetes mellitus (T2DM) [1]. Healthy eating may lower hemoglobin A_1c_ (HbA_1c_) to a similar extent as medical treatments for T2DM [2,3]. In some cases, healthy eating can put the disease in remission [4-12]. However, people with T2DM indicated that implementing healthy eating recommendations in their everyday lives is challenging [5,7,8].

Several strategies are available to support people with T2DM with healthy eating. The strategies approach healthy eating in dissimilar manners that could be broadly categorized as dietary prescription, lifestyle counseling, and behavioral therapies [13]. Dietary prescription is characterized by a “top-down” and biomedical approach: the therapist actively provides the solution in the form of a strict calorie-restricted diet, and the main goal is to achieve weight loss or improved HbA_1c_ levels (eg, [12]). In lifestyle counseling, the participant has a more active role: the therapist provides lifestyle education, meal plan templates, and personalized advice to implement nutritional recommendations. The main goal is adherence to a healthy lifestyle (eg, the Look AHEAD [Action for Health in Diabetes] trial [14] and the Diabetes Remission Clinical Trial [DIRECT]; [15]). Behavioral counseling is characterized by a more “bottom-up” and holistic approach: the starting point is the participant’s preferences; the goals and approaches are collaboratively planned. The therapist has an enabling role in the process: stimulating the participant’s problem-solving abilities and self-efficacy by motivating and supporting the participant. The main goal is achieving a mindset that favors healthy lifestyle behaviors (eg, [16]).

All of these strategies have been successful in initiating health benefits such as weight loss and improved HbA_1c_ levels [12,16,17] but have struggled with maintaining the benefits in the long term [8,18-21]. Even after the most well-known T2DM interventions—the Look AHEAD [14] and the DIRECT trial [15]—health benefits gradually disappeared. The Look AHEAD trial (restricted caloric intake using portion-controlled meal plans, calorie-counting techniques, and meal replacements combined with moderate physical activity) demonstrated average weight loss of 8.6% (SD 6.9%) in the intervention participants, but half of the initial weight loss was regained after 5 years of follow-up [22,23]. The DIRECT trial (a very low–calorie diet, followed by stepwise food reintroduction) demonstrated that almost half of intervention participants achieved T2DM remission at 12 months, but this percentage declined to 36% at 24 months [24].

Most previous studies used dietary description or lifestyle counseling strategies. These strategies either included strict (ie, very low–calorie) diets or were performed in highly controlled research settings (intensive intervention regarding diet and physical activity combined with frequent contact with health care providers) [12,25,26]. However, people may experience difficulties when they return from these clinical and controlled research settings to their everyday lives. In everyday life, healthy eating requires a scale of personal and social resources, ranging from practical cooking skills to personal agency [27-29]. It is not only about *what* people eat but also *why* and *how* they eat: the ability to prepare food, social economic resources, the food environments, social support, self-image, mental health, etc. This may explain why the Mediterranean diet is considered as one of the healthiest diets with (long-term) health benefits [30]; the Mediterranean diet is not a strict diet, rather *a way of life* that includes seasonal cooking, freshly cooked meals, and socializing with others [31].

### Objectives

Hence, there seems to be a need for a strategy with an eye for everyday life of people with T2DM to promote long-term healthy eating. A health theory centered around the everyday life context is salutogenesis. Applying salutogenesis to nutritional research leads to the assumption that healthy eating is not regarded as a central goal in life but as a resource for greater enjoyment of life [32]. It requires to accept a holistic viewpoint on health and real-life complexity as starting points for conducting and evaluating nutritional interventions. In salutogenesis, health results from the continuous everyday life interactions between the individual and the social, economic, cultural, physical, mental, and biochemical stressors [33]. The central concept in salutogenesis is the sense of coherence (SoC), which is the individual capability to mobilize and use health-promoting resources [33]. Understanding the *resources* that facilitate coping with these stressors in a health-promoting manner can help to unravel underlying principles of creating health [34]. Salutogenesis guided the development of the Salutogenic Intervention for Type 2 Diabetes (SALUD) program [35].

The aim of this study protocol is to outline the randomized controlled trial (RCT) in which the SALUD program is compared with the Dutch usual care for T2DM. The theoretical principle behind the program is mobilizing 2 important psychosocial resources required for organizing healthy eating and improved well-being in everyday life: self-identity and social support [35]. The present hypothesis is that mobilizing these resources will initiate a process of empowerment, leading to improved food literacy (direct effect) and improved health (indirect effects). Food literacy is the capability to navigate different food situations to make healthy eating choices [36], which is important for healthy eating and well-being in the long term. It is a measure that combines all relevant aspects for healthy eating in everyday life, that is, knowledge, skills, and behaviors. Hence, the primary objective is to determine the effect of the SALUD intervention on food literacy. Diet quality as well as several physical and psychosocial outcomes will be evaluated as secondary outcomes.

## Methods

### Study Design

A 2-arm, semiblinded RCT will be conducted with 56 people with T2DM in the Netherlands. The whole study duration will be 24 weeks, with measurements planned at baseline (T0), after 12 weeks (postintervention; T1), and 24 weeks (follow-up; T2). Participants will be randomly allocated to the intervention group (SALUD program) or to the control group (usual T2DM care [37]). The SALUD program will consist of 1 individual intake session (at the start), group sessions for 12 consecutive weeks, and 1 booster session (at 24 weeks). The study procedure is outlined in Figure 1.

**Figure 1 figure1:**
[figure not shown]
Salutogenic Intervention for Type 2 Diabetes (SALUD) study procedure.

### Ethics Approval

Medical Ethical Committee Oost-Nederland has granted medical ethics approval for this study on August 8, 2021 (Medical Ethical Committee number 2021-12949).

### Trial Registration

The study has been registered at Netherlands Trial Registry with registration number NL8963 [38] (registered on October 12, 2020).

### Participants

The target population consists of Dutch-speaking men and women with T2DM. Inclusion criteria are as follows: officially diagnosed with T2DM by a general practitioner (GP); aged ≥18-75 years; fluent in Dutch, competent to make own decisions; and in possession of a computer device with internet connection. Exclusion criteria are as follows: pregnant, lactating, or intention to become pregnant in the upcoming 6 months; severe chronic illnesses or condition or comorbidities (other than T2DM, eg, kidney failure, severe form of chronic obstructive pulmonary disease [gold III or IV], heart failure [class 2-4], cancer, dementia, or severe depression); bariatric surgery in the past; and eating disorders (eg, anorexia or bulimia).

### Recruitment

Participants are recruited via posters in GP practices, advertisements in local papers, social media, and websites of national diabetes organizations. In addition, several local GPs and practice nurses approach clients during regular health appointments or via phone or mail. Before commencement, all participants receive the information brochure that explains the study in detail and a phone call from the investigator for further explanation. At least 7 days after the phone call, participants sign an informed consent form and send it to the investigators before the start of the study. Participants are informed (written and verbally) that they will be randomly allocated to either the intervention or control group.

### Randomization and Blinding

Randomization of participants will be performed by an independent researcher (not involved in the study) with use of a web-based randomization tool. The data analysis for the primary outcome will be run blinded by an independent researcher. Treatment codes will be broken after finalization of the data analyses. Participants and researchers are not blinded during the measurements owing to the nature of the intervention.

### Intervention: SALUD Program

#### Theory Operationalization

For the development of the SALUD program, 3 main principles of salutogenesis were operationalized:

The participant as a whole: in salutogenesis, health is a complex and dynamic concept incorporating multiple aspects of well-being that relate to the whole person [39]. This requires interventions that aim to improve multiple aspects of health. Hence, in the SALUD program, physical and psychosocial health are valued equally.The participant’s active involvement: to facilitate the mobilization of health resources, intervention strategies should be adjusted to real life to increase the chance of successful implementation of newly adopted behaviors in everyday life. This can only be done successfully and respectfully when people with T2DM and their health care providers are actively involved in the development of interventions. Hence, people with T2DM, health care professionals, and scientists of different disciplines provided their perspectives multiple times during intervention development (the participatory developmental process has been described by Polhuis et al [35]). The participatory developmental process revealed that self-identity, social support, food literacy, disease acceptance, and stress management were crucial resources to enable healthy eating in everyday life.The participant’s individual learning process: salutogenesis complements traditional information-providing approaches by supporting individuals in a learning process to mobilize personal and environmental health-promoting resources to cope with stressors. Hence, the strategy of the intervention was to enhance the generalized resistance resources (GRRs) and specific resistance resources (SRRs) for enabling healthy eating through a reflective and empowering approach. The main strategy was based on mobilizing the GRRs self-identity and social support; session themes were based on the identified SRRs food literacy, disease acceptance, and stress management (Table 1).

**Table 1 table1:** Summary of the Salutogenic Intervention for Type 2 Diabetes (SALUD) program sessions.

Session topic	Setting	Goals
0. Intake	Coach and participant one on one (web-based)	Getting to know the participant; personal history, motivations, and goals
1. Building trust	Coach and peer-group (web-based)	Establishing a safe place Social bonding
2. Goal setting	Coach and peer-group (web-based)	Formulating at least one personal Specific, Measurable, Achievable, Relevant, and Time-Bound (SMART) health goal
3. Food literacy I	Coach and peer-group (web-based)	Reflection Question hour with a dietician Setting up an individualized diabetes-proof week menu Practical skills for meal planning, grocery shopping, and cooking
4. Food literacy II	Coach and peer-group (web-based)	Reflection Learning and sharing recipes (SALUD recipe book)
5. Stress management	Coach and peer-group (web-based)	Reflection Stress management Diabetes-related stress Mindfulness exercises (body scan and breathing exercises)
6. Nature break	Coach and peer-group (web-based)	Reflection Stress management Boosting positive emotions A mindful, individual walk outside (20 minutes)
7. Measuring progress	Coach and peer-group (web-based)	In-depth reflection, evaluation, and adjustment of health goals Social support
8. Social support	Coach and peer-group (web-based)	Involve partner or friend in the health process Opportunity for partners or friends to ask questions about program or health Social support
9. Self-identity	G Coach and peer-group (web-based)	Reflection Why do you eat what you eat? Values and life goals Disease acceptance Social support: question hour with role model
10. Open session	Coach and peer-group (web-based)	The participants choose the topic of this session during session 7
11. Measuring progress	Coach and peer-group (web-based)	In-depth reflection, evaluation, and adjustment of health goals Social support Long-term health strategies
12. Festive closure	Coach and peer-group (web-based)	Reflection on personal learning trajectory Boosting positive emotions Long-term health strategies
13. Booster session	Coach and peer-group (web-based)	Reflection and sharing of experiences over the past 12 weeks Social bonding Long-term commitment to a healthy lifestyle

#### Setting

The SALUD program takes place in a web-based group setting (7-8 participants per group) under supervision of a certified and experienced lifestyle coach. The communication platform Microsoft Teams (Microsoft) is used for hosting the sessions. The job of lifestyle coach in the Netherlands entails coaching and motivating people to sustainable lifestyle changes regarding nutrition, physical activity, sleep, and stress. Certified lifestyle coaches are extensively trained in various communication and coaching techniques. They have basic knowledge of lifestyle-related diseases, physiology, and nutrition. The current coach has been externally hired for the study by the authors and is not part of the research team. The coach is specifically experienced in group coaching (>5 years), particularly people with T2DM. The participants will be divided into separate groups on different days (based on their availability), all under supervision of the same coach.

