### Control: Usual T2DM Care

The participants in the control group receive the usual Dutch T2DM care according to the Dutch General Practitioners Association (Nederlands Huisartsen Genootschap) protocols [37]. The usual care of T2DM is based on medical treatment, education, and lifestyle advice. Newly diagnosed persons and persons who require insulin administration are referred to a dietician by the GP. In some cases, the GP recommends a referral to a psychologist for help with dietary advice or to a physical therapist to help with physical activity. The GP refers to a specialist in case of complications (such as retinopathy and nephropathy). Generally, a person with T2DM has 4 quarterly checkups with the practice nurse and 1 yearly checkup with the GP. However, the exact frequency of the appointments depends on the specific agreements between the health care provider and the patient.

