### Sample Size Calculation

Sample size calculation is based on the known mean value and SD of the SPFLS (food literacy measure) for the Dutch general population [36]. There are no RCTs with lifestyle interventions in the scientific literature that assessed food literacy (measured with SPFLS or another measure for food literacy) as a primary outcome. However, as RCTs evaluating lifestyle interventions that targeted psychosocial outcomes such as self-efficacy have demonstrated effect size of between 1.1 and 1.7 [48,49], it seemed reasonable to expect an effect size of 0.9. With use of the Cohen *d* calculation for effect size, an anticipated mean of 4.20 SPFLS score in the intervention group, and an anticipated mean of 3.83 (SD 0.41) in the control group is expected at T1 (based on references values [36]). With a standard power of 80% and a significance level of 5%, a total of 19 participants per group (38 participants in total) are needed. Adding a 30% dropout rate, the ideal sample size was set at 28 participants per group (56 in total).

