According to a strict data analysis protocol, primary and secondary outcomes are tested with mixed models. Secondary outcomes are also tested if the primary outcome is not statistically significant. The analyses scripts will be written by the researchers; the analysis of the primary outcome will be run by an independent researcher who is blind to the intervention code. Assumptions for mixed models are checked. The mixed models will test the difference compared with baseline in the scores and values (ie, dependent variables) between intervention and control (ie, independent variable) at T1 and T2. Fixed effects are the treatment condition, time, and the covariates; random effects are the repeated measures per participant at T0, T1, and T2. Multiple models are tested; a crude model, and additional models that are adjusted for confounders commonly adjusted for in literature (eg, sex, age, education, and BMI). Variables that statistically significantly differed at baseline are also included in a model as covariates. The final results are presented in a table displaying the estimated marginal means, 95% CIs, and *P* values for the treatment effect for all primary and secondary outcomes.

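### Only the SALUD arm is treated in peer groups, but the sample size and mixed model assume independent participants; if outcomes correlate within groups, standard errors are too small

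*Protocol article*

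**What the plan says.** The Setting subsection of the protocol article describes group delivery: "The SALUD program takes place in a web-based group setting (7-8 participants per group) under supervision of a certified and experienced lifestyle coach". It adds: "The participants will be divided into separate groups on different days (based on their availability), all under supervision of the same coach". With 28 people allocated to the program, this gives about 4 groups.

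Controls are not grouped: "The participants in the control group receive the usual Dutch T2DM care according to the Dutch General Practitioners Association".

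The Sample Size Calculation assumes that SALUD participants will average 4.20 on the SPFLS. For the comparator it has "an anticipated mean of 3.83 (SD 0.41) in the control group is expected at T1". From these values it derives the number needed: "With a standard power of 80% and a significance level of 5%, a total of 19 participants per group". A 30% dropout allowance raises this to 28 per group. It is the only inflation applied.

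Under Statistical Analyses, the fixed effects are treatment condition, time and covariates. On the rest of the model the text says: "random effects are the repeated measures per participant at T0, T1, and T2". The article contains no ICC, no design effect and no term for the coaching group.

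**The concern.** The program's main strategy includes mobilising social support. All 12 weekly sessions and the booster are held in the peer group, with bonding and exchange among the stated goals, and each group chooses the topic of session 10. Members of one group share these experiences, and members of different groups do not. Their outcomes at T1 and T2 may therefore be more alike within a group than between groups, while each control stands alone.

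A model with participant-level random effects only cannot see that similarity. It would treat 28 intervention participants as 28 independent pieces of information. The variance of the intervention mean would be understated, confidence intervals would be too narrow, and the primary comparison would reject a true null more often than 5%. The error runs toward false positives. A test that used the correct standard error would have less power than the independence calculation implies.

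**Working it through.** **Inputs**
- Means 4.20 and 3.83, SD 0.41, two-sided 5%, power 80%, dropout 30%, 28 per arm (Sample Size Calculation, Statistical Analyses).
- Groups of 7-8 (Setting). 28/7 = 4 groups.
- Analysed per arm at the planned dropout: 28 × 0.70 = 19.6, or 19.6/4 = 4.9 per group.
- ICC ρ: not in the document. Assumed values are 0.02, 0.05 and 0.10.

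**Step 1: reproduce the stated size**
- d = (4.20 − 3.83)/0.41 = 0.902.
- n = 2(1.960 + 0.842)²/0.902² = 19.3 per arm. The stated 19 agrees within rounding (20 if rounded up).
- 19/0.70 = 27.1, rounded up to 28.

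The figure follows from the independent-observations formula and leaves no room for a design effect.

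**Step 2: variance and type I error**

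With groups of size m in one arm only, the variance of the arm difference is σ²[(1 + (m − 1)ρ)/n + 1/n]. Divided by the independence value 2σ²/n, this gives

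F = 1 + (m − 1)ρ/2.

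The actual type I error of a test that ignores the groups is 2[1 − Φ(1.960/√F)]. For 4 groups of 7:

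| ICC (assumed) | F | true SE / naive SE = √F | 1.960/√F | type I error |
|---|---|---|---|---|
| 0.02 | 1.06 | 1.030 | 1.904 | 5.7% |
| 0.05 | 1.15 | 1.072 | 1.828 | 6.8% |
| 0.10 | 1.30 | 1.140 | 1.719 | 8.6% |

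A simulation of an ordinary t test (40,000 runs, 28 per arm, 4 groups) gave 6.7% at ICC 0.05 and 8.6% at 0.10. With 4.9 per group, F is 1.0975 and 1.195, and the type I error is 6.1% and 7.3%.

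**Step 3: power at d = 0.90 when the standard error is correct**

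Noncentrality is δ = 0.90/√(2F/n). The first power column uses a t distribution with 2n − 2 degrees of freedom. The last uses Satterthwaite degrees of freedom, df = (v₁ + v₂)²/[v₁²/(4 − 1) + v₂²/(n − 1)], where v₁ = (1 + (m − 1)ρ)/n and v₂ = 1/n. No baseline adjustment is made.

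| n per arm | ICC (assumed) | δ | power, 2n − 2 df | Satterthwaite df | power, Satterthwaite |
|---|---|---|---|---|---|
| 19.6 | 0 | 2.82 | 78% | 10.3 | 72% |
| 19.6 | 0.05 | 2.69 | 75% | 9.1 | 67% |
| 19.6 | 0.10 | 2.58 | 71% | 8.2 | 62% |
| 28 | 0 | 3.37 | 91% | 10.8 | 86% |
| 28 | 0.05 | 3.14 | 87% | 8.8 | 80% |
| 28 | 0.10 | 2.95 | 83% | 7.6 | 73% |

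A test that ignores the groups would hardly show this loss. In simulation at 19 per arm and d = 0.902 it rejected in 77.3%, 76.6% and 75.6% of runs at ICC 0, 0.05 and 0.10, but only because its type I error had risen.

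**Step 4: what 4 groups can estimate**

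In simulation of 4 groups of 7 and 28 controls (200,000 runs), the group variance came out as zero in about 54% of trials at ICC 0.02, 47% at 0.05 and 38% at 0.10. The nested model did hold type I error, at about 3.8-4.2% for ICC 0.02-0.05.

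**The case against.** A reader might infer that the standard errors are certainly too small and that real power is certainly below 80%. The documents do not support either statement without conditions.

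- **No ICC is given.** At ICC 0.01 the type I error is about 5.3%, which is negligible, and at zero there is no bias. Some features also limit variation between groups: a single coach leads every group, a manual is used, the coach completes weekly evaluation forms and has weekly checkups with the principal investigator, and goals are personal. Because there is only one coach, no coach effect can be separated from treatment; the cluster is the group. This objection stands as far as size is concerned. It does not make independence a safe default, given the weight the program puts on peer interaction.
- **Not all of the power shortfall comes from clustering.** At 19.6 per arm, power is already about 78% with no clustering. At ICC 0.05, most of the further drop to 67% comes from the degrees of freedom of the corrected analysis (78% to 75% to 67%). At ICC 0.10 it is more than half (78% to 71% to 62%). This stands.
- **The shortfall depends on full dropout.** With 28 analysed per arm, power before the degrees-of-freedom correction exceeds 80% at both ICCs. Adjustment for baseline could also help, though group effects that arise after baseline would remain. This stands for power but does not touch the type I error, which grows with group size.
- **A separate analysis protocol may exist.** The article refers to one that is not shown, and it may contain a group term. But the article does state the random-effects structure and the full basis of the sample size, so the point concerns what is written and not missing detail.

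**Conclusion.** The point holds in conditional form. The plan states a sample size and a mixed model that assume independent participants, although the intervention arm alone is treated in about 4 interactive peer groups. If outcomes correlate within groups, the standard error of the primary comparison is too small: the true value is about 3%, 7% or 14% larger at assumed ICCs of 0.02, 0.05 and 0.10 with groups of 7, and the type I error is about 5.7%, 6.8% and 8.6%.

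At the planned dropout, power is about 75% at ICC 0.05 and 71% at 0.10, against 78% without clustering. With Satterthwaite degrees of freedom it is about 67% and 62%, against 72% at ICC zero. If all 28 per arm are analysed, the stated 80% is met at ICC 0.05 and 0.10 before the degrees-of-freedom correction. After it, power is about 80% and 73%.

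These sizes rest on assumed ICCs, 4 equal groups, d = 0.90 and no baseline adjustment. The absence of a group term from the stated model is certain; the size of the consequence is not.

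**What to change.** - **Primary model.** Fit a partially nested mixed model: add a random SALUD-group effect for intervention participants at T1 and T2, treat each control as their own unit, and use Satterthwaite or Kenward-Roger degrees of freedom. Apply the same structure to the secondary outcomes.
- **Reporting.** Give the estimated ICC. Because the group variance will often be estimated as zero with 4 groups, always report a sensitivity analysis of the T1 result over fixed ICCs (for example 0.02-0.10), whatever the estimate. The fixed values are assumptions and should be labelled so.
- **Sample size text.** Restate the 80% power over the same ICC range and state the assumed number analysed. Data acquisition ended on August 1, 2022, so this cannot change enrolment; it belongs with the stated limitations. The article expects the analysis at the end of 2023, so at the time of the article the model could still be changed.

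**Cost.** One extra random term and some wording; group membership should already be on record. The price is wider intervals, a poorly estimated group variance, a somewhat conservative test at low ICC, and a less favourable stated power.
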